#### Moderators

2.6.3

##### Patient motivation

2.6.3.1

Patient motivation is assessed using the Motivation to Engage in Treatment (MET) scale of the Treatment Motivational Scales for forensic outpatient treatment (TMS-F) developed by Drieschner and Boomsma (2008a). This self-report questionnaire comprises 85 statements designed to gauge the motivation of forensic patients for engaging in outpatient treatment. Beside the MET scale, the TMS-F encompasses six Internal Determinants (ID) scales and a social desirability scale. The MET scale serves as a measure for Patient Motivation, Drieschner and Boomsma (2008b) conclusion that in particular the MET scale predicts treatment engagement to a substantial degree. The MET scale contains 16 items (e.g., “I would stop therapy if I see no change in my life”), each scored on a 5-point scale ranging from 1 “totally disagree” to 5 “totally agree.” Drieschner and Boomsma (2008a) found that the MET scale demonstrate adequate internal consistency, with the sum score of the items being reliably measured (*α* = 0.88) for most purposes.

##### Therapist motivation

2.6.3.2

Therapist motivation is measured with a self-constructed questionnaire, the Therapist Motivation Questionnaire (TMQ). The TMQ consists of 13 items (e.g., “I experience positive emotions while giving treatment sessions to my patient”) pertaining to various aspects, such as experiencing a positive relationship with the patient, having self-assurance in one’s abilities, exerting effort to assist the patient with their issues and actively involving the patient in the treatment process. Answering categories vary on a 6-point scale from 1 “totally disagree” to 6 “totally agree.” High scores reflect increased motivation.

#### Other materials and measurements

2.6.4

##### Virtual reality software

2.6.4.1

The VR-CBT software utilized in this study was collaboratively developed by CleVR^1^ in conjunction with researchers from various academic institutions, mental health facilities, child and adolescent psychiatry and forensic psychiatry. CleVR’s VR-CBT software has a CE mark of quality as a medical device and can be safely used as a medical aid within (mental) healthcare. The VR-CBT software enables the creation of personalized scenarios and interactive virtual (social) worlds.

Accompanied by a comprehensive manual (Social Worlds 4.1), the VR software empowers the therapist to govern the virtual environment through a laptop. During the VR session, the patient wears Oculus Rift VR glasses (type S, v1.2), fully encompassing their field of view and allowing complete immersion in the virtual environment. Concurrently, the therapist observes the same virtual setting on a computer screen, facilitating seamless communication with the patient via headphones connected to a microphone. This control encompasses adjusting characters’ behavior within the virtual realm, including actions like approaching, arm movements and gaze, as well as regulating their emotional expressions, such as displaying anger. To further enhance the immersive experience, a dual-joystick configuration allows the patient to navigate within the virtual environment while simultaneously providing real-time visual feedback of hand movements in the simulated world. Moreover, the therapist can manipulate the characters’ voices by utilizing a voice shaper integrated with the MorphVox Pro program.^2^

The VR session begins as the patient put on the VR glasses and headphones, and if needed, holds the joysticks. At the outset, the patient is introduced to a “virtual waiting room,” which serves as a neutral and low-stimulation environment, allowing them to adapt to the VR setting. Once the patient feels at ease, the therapist proceeds to load the targeted VR environment, and the role-playing or exercise commences. Importantly, throughout the VR session, the therapist retains the ability to “pause” the experience, accomplishing this by deactivating the voice modifier and directly communicating with the patient using their own voice within the virtual environment. Figure 2 shows some examples of virtual environments.

**Figure 2 fig2:**
[figure not shown]
Virtual environments: shopping street **(A)**, office **(B)**, and bus **(C)**. Source: CleVR B.V., Delft, the Netherlands.

##### Program integrity

2.6.4.2

To check whether the study protocol in both conditions has been carried out according to the design, the therapist keeps a Program Integrity checklist in which the therapist records several aspects for each module, including the number of (analog or VR) role-play exercises conducted per session, the total sessions with and without role-play and whether the patient engaged in the role-plays in both a relatively relaxed state and a tense state, among other factors. In addition, the therapist is asked to report all details, including whether and why deviations from the protocol occurred and whether other therapy sessions were conducted that were not prescribed in the module.

##### Feedback on study protocol

2.6.4.3

To gather feedback on the study protocol, the Re-ART final evaluation form is employed. This form is a standard part of the Re-ART treatment, with versions for both patients and therapists. For the purposes of this study, modifications have been made to the forms. Questions related to feasibility and usability were added, while questions not relevant to the study were removed. Instead of administering the forms at the end of the Re-ART treatment, they will be given at the conclusion of the study.

### Data management

2.7

Data relevant to the study will be stored in a distinct research file, accessible only to the researchers involved in the study. To ensure security, SPSS files will be stored in a protected Citrix environment. During data entry into SPSS, researchers will use unique codes to differentiate subjects. These codes can be cross-referenced with a separate password protected Excel spreadsheet to identify individual subjects. The linkage between subject codes and patient files will be exclusively accessible to the researcher team, maintaining confidentiality and data integrity.

#### Statistical analyses

2.7.1

The data analysis will be conducted using IBM SPSS v29. The analytical plan aims to examine the effectiveness of Re-ART with VR (Re-ART VR) compared to standard Re-ART in a forensic outpatient setting. Intention to Treat (ITT) analyses as well as Per Protocol (PP) analyses will be conducted. The ITT analyses will include data from all randomized patients, regardless of drop-out, whereas PP analyses will include only those patients who completed the treatment as originally allocated.

To evaluate treatment effects on primary and secondary outcomes, a Repeated Measures Analysis of Covariance (RM-ANCOVA) will be performed. This approach allows to account for both baseline scores and time, along with other potential covariates, thus providing a more precise estimation of the intervention effect.

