#### Sample size

2.3.1

To ensure sufficient statistical power for detecting significant effects in our repeated measures ANCOVA with within-between interaction, an *a priori* power analysis was conducted (G*Power; Faul et al., 2009). Using an expected effect size (f) of 0.25, a significance level (α) of 0.05, and a desired power (1-β) of 0.80, the calculation revealed that a total sample size of 34 participants is required for the study (17 in each condition). The analysis assumes two groups (Re-ART VR vs. regular Re-ART) with two measurement points (pre- and post-intervention), a correlation of 0.5 among repeated measures, and no sphericity correction (ε = 1).

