##### Primary outcome analysis: degree of aggression regulation

2.7.1.2

An RM-ANCOVA will be conducted with the FSI-R scores at both pre- and post-intervention as the within-subjects factor. The treatment condition (Re-ART VR vs. regular Re-ART) will serve as the between-subjects factor. Covariates like age, motivation level, and risk of recidivism will be included to control for initial differences.

The primary focus will be on the interaction term between treatment condition and time to examine whether the rate of improvement in aggression regulation differs between the two conditions.

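### The primary RM-ANCOVA is said to account for baseline, but its condition-by-time test compares change scores; adjusting for T1 would cut error variance by about 25% at the plan's own correlation

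*Protocol article*

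**What the plan says.** Section 2.7.1 (Statistical analyses) chooses an RM-ANCOVA for the primary and secondary outcomes. It justifies the choice by saying "This approach allows to account for both baseline scores and time", together with other covariates, and concludes that the effect is estimated more precisely.

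Section 2.7.1.2 (primary outcome) then sets out the model: "An RM-ANCOVA will be conducted with the FSI-R scores at both pre- and post-intervention as the within-subjects factor". Condition is the between-subjects factor, and the term of interest is condition by time. On covariates it says: "Covariates like age, motivation level, and risk of recidivism will be included to control for initial differences". The T1 FSI-R score is not named as a covariate there, nor among the background variables in section 2.7.1.1. Section 2.7.1.3 repeats the structure for the BITI and the Impulsivity subscale.

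Section 2.3.1 (Sample size) powers the trial for a "repeated measures ANCOVA with within-between interaction", with two groups, two time points, a pre-post correlation of 0.5 and 34 patients in total.

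**The concern.** When there are only two time points, the condition-by-time term in a repeated measures model is algebraically the between-arm difference in T2 minus T1, adjusted only for whatever covariates are entered. The T1 score is part of the outcome. It is removed with a slope fixed at 1, whereas its regression slope on T2 is the pre-post correlation (equal variances assumed), which the plan takes to be 0.5.

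Two things follow. First, change scores over-correct chance differences at baseline. An arm that happens to start worse will appear to improve more through regression to the mean. Second, change scores are less precise than an analysis of T2 that adjusts for T1, so the precision claimed in section 2.7.1 is not delivered by the model in section 2.7.1.2.

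Both matter in a trial of 17 per arm. Section 3.2 already concedes that 34 patients may be too few for small but clinically relevant differences, and the Bonferroni correction in section 2.7.1.6 tightens alpha further.

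**Working it through.** **Inputs, all from section 2.3.1.** Effect: "Using an expected effect size (f) of 0.25". Alpha: "a significance level (α) of 0.05". Power: "a desired power (1-β) of 0.80". N = 34 (17 per arm), two groups, m = 2 time points, correlation ρ = 0.5, ε = 1. Variances below are in units of the outcome SD², with equal SDs at T1 and T2.

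**1. Reproduce the planned sample size.** For the within-between interaction, λ = f²·N·m/(1−ρ) = 0.0625 × 34 × 2 / 0.5 = 8.5, with 1 and 32 df. Power is 0.807 at N = 34 and 0.781 at N = 32, so 34 is the smallest balanced total. The plan's figure reproduces, which confirms that the plain interaction is the test that was powered.

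**2. Effect size this implies.** For a difference δ in mean change with per-patient variance V, λ = δ²/(4V/N). With V = 2(1−ρ) = 1.00, δ² = 8.5 × 4/34 = 1.0, so δ = 1.0 SD.

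**3. Error variance of each analysis.**
- T2 alone: 1.00
- Change score: 2(1−ρ) = 1.00
- T2 adjusted for T1: 1−ρ² = 0.75

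At ρ = 0.5 the change score is no more precise than ignoring T1 altogether. The ratio of adjusted to change-score variance is (1−ρ²)/[2(1−ρ)] = (1+ρ)/2 = 0.75, and it is below 1 for every ρ below 1.

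**4. Power at N = 34 for a 1.0 SD effect** (32 df for change, 31 for ANCOVA):

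| ρ | Change variance | ANCOVA variance | Saving | Power, change | Power, ANCOVA |
|---|---|---|---|---|---|
| 0.3 | 1.40 | 0.91 | 35% | 0.67 | 0.84 |
| 0.5 | 1.00 | 0.75 | 25% | 0.81 | 0.90 |
| 0.7 | 0.60 | 0.51 | 15% | 0.95 | 0.98 |
| 0.8 | 0.40 | 0.36 | 10% | 0.99 | 1.00 |

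At ρ = 0.5 the effect detectable with 80% power falls from 0.99 to 0.86 SD. Equivalently, the total N for 80% power falls from 34 to 26.

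**5. Finite-sample check.** The 25% ignores the cost of estimating the slope. A simulation of 20,000 trials at N = 34 and ρ = 0.5 gave a variance ratio of 0.778 (a saving of about 22%) and power of 0.811 against 0.897.

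**6. Chance imbalance.** The baseline difference between arms has SD √(2/17) = 0.34. An imbalance of 0.5 SD is 0.5/0.34 ≈ 1.46 standard errors, and one at least that large in either direction occurs in about one trial in seven. Given an imbalance d, the expected change-score difference moves by (1−ρ)d = 0.5 × 0.5 = 0.25 SD, a quarter of the planned effect. ANCOVA removes that shift.

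**7. Adding T1 to the planned model.** In the same simulation, entering T1 as a covariate in the change-score model gave the same t statistic for condition as the ANCOVA of T2 on T1, to rounding error.

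**The case against.** The strongest reply is that the text does not rule baseline adjustment out. The covariate list in section 2.7.1.2 is open-ended, and section 2.7.1 can be read as counting baseline scores among the covariates. If T1 FSI-R were entered, the condition-by-time test would be identical to the ANCOVA (step 7). This stands as a reason why the repair is small. It does not settle the point: the T1 score is the one covariate that matters most, it is not named, and the sample size was computed for the interaction without it.

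Second, the planned test is valid. Under randomization it is unbiased on average, has the right type I error, and is the test for which N = 34 was calculated. That is correct. The bias in step 6 is conditional on an observed imbalance, and 0.5 SD is an illustrative size, about 1.5 times the SD of the baseline difference.

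Third, the size of the gain is not fixed. It depends on ρ, for which 0.5 is a planning assumption, and it is 22% rather than 25% at N = 34. The power comparison also leaves out motivation and recidivism risk, which could recover part of the loss if they correlate with baseline FSI-R. This stands, but the effect is modest. Suppose a covariate correlates 0.4 with T1 and relates to T2 only through T1 (correlation 0.4 × 0.5 = 0.2). Its covariance with change is then 0.2 − 0.4 = −0.2, so the change-score variance falls to 1.00 − 0.04 = 0.96. T1 adjustment still gives 0.75, a ratio of 0.78; simulation with such a covariate at N = 34 puts the remaining saving at about 18%.

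**Conclusion.** The concern holds. The model written in section 2.7.1.2 compares change scores and does not account for baseline in the sense that section 2.7.1 claims. At the plan's own correlation it gains no precision from T1 at all. Adjusting for T1 would lower the error variance by 25% in large samples and by about 22% at N = 34, raising power for the planned 1.0 SD effect from 81% to about 90%.

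These figures assume ρ = 0.5, equal variances at T1 and T2, complete data, alpha 0.05 and no other covariates. The direction does not depend on the value of ρ. The issue is efficiency, sensitivity to chance imbalance and a wrong description of the method; it does not invalidate the planned test. It should be changed before the data are analysed.

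**What to change.** Prespecify the primary analysis as an ANCOVA of the T2 FSI-R Aggression plus Anger score on condition, with the T1 score as a named covariate alongside a fixed list of other baseline covariates. Report the adjusted difference with its 95% confidence interval. A mixed model with the arms' baseline means constrained to be equal serves the same purpose. Use the same form for the BITI and Impulsivity, each with its own T1 score.

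If the repeated measures layout in SPSS is kept, name the T1 score explicitly as a covariate; the condition-by-time test then matches the ANCOVA. If neither change is made, section 2.7.1 should at least be reworded to say that the analysis compares change from baseline and does not adjust for it.

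The cost is wording and one degree of freedom. No new data are needed, and N = 34 need not change.

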##### Preliminary analyses

2.7.1.1

Before conducting the main analyses, the data will be inspected for missing values (e.g., MCAR—Missing Completely At Random), outliers, and the assumptions of RM-ANCOVA, including sphericity, homogeneity of variances, and linearity. Missing data will be addressed using multiple imputations (Expectation Maximization—EM), and outliers will be examined and treated to ensure they do not bias the results.

To verify the randomization results, various background variables such as age, migration background, and primary diagnosis will be compared between patients in Re-ART VR and regular Re-ART using chi-square tests for dichotomous measures and independent *t*-tests for continuous measures. These variables will be included as covariates in the RM-ANCOVA if significant differences are found.

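### The plan names Expectation Maximization as its multiple imputation; if the ITT analysis is run on one EM-filled data set, its inference is invalid once T2 scores are missing

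*Protocol article*

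**What the plan says.** Section 2.7.1.1 (Preliminary analyses) fixes the handling of missing values in one clause: "Missing data will be addressed using multiple imputations (Expectation Maximization—EM". EM is the only technique it names.

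Three other statements determine how much depends on that clause:

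- Section 2.7.1: "The ITT analyses will include data from all randomized patients, regardless of drop-out".
- Section 2.7.1.2, on the RM-ANCOVA with pre and post scores: "The primary focus will be on the interaction term between treatment condition and time".
- Section 2.7.1: "The data analysis will be conducted using IBM SPSS v29".

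Section 2.7.1.5 describes sensitivity analyses that vary the covariates only. No other section corrects the wording or says that several completed data sets will be pooled.

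**The concern.** Multiple imputation draws several completed data sets with random error, analyses each and pools them, so that uncertainty about the missing values enters the standard error. EM is a maximum-likelihood algorithm. When it is used to fill data, it puts one conditional expected value in each gap. A later RM-ANCOVA treats those values as observations: they carry no residual scatter, and they count fully towards the degrees of freedom.

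The primary ITT result depends on this choice. A two-time-point RM-ANCOVA needs both scores, so a patient without a T2 score enters the ITT analysis only through a filled-in value. The article itself describes routes to a missing T2 score. Participation ends if another intervention has to be given (section 2.5), and a patient who cannot continue VR because of cyber sickness is taken out of the study (section 2.5.1). The second route exists in one arm only. The covariate-based sensitivity analyses would not expose an error in the imputation.

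**Working it through.** **Inputs from section 2.3.1.** f = 0.25, α = 0.05, power 0.80, two groups, two time points, correlation 0.5, 34 patients (17 per arm).

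**Input not in the article.** The dropout rate. I assume 2, 4 or 6 of 17 per arm missing at T2 (11.8%, 23.5%, 35.3%), completely at random.

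**Step 1: the plan's own figure.** For the within-between interaction, λ = f²·N·m/(1−ρ) with 1 and N−2 degrees of freedom. At N = 34, λ = 0.0625 × 34 × 2 / 0.5 = 8.5 and power is 0.807. At N = 32, power is 0.781. The stated 34 reproduces and is not in dispute.

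**Step 2: effect scale.** With unit SD at each time, the SD of change is √(2(1−0.5)) = 1. A 1.0 SD difference in change has SE √(2/17) = 0.343, and (1/0.343)² = 8.5. So 1.0 SD is the planned effect.

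**Step 3: simulation.** 3,000 trials per setting, bivariate normal T1/T2. The condition × time test is a t-test on change. EM fill is the regression prediction from observed cases, with or without arm as a predictor. Genuine multiple imputation uses 20 imputations with arm and T1 in the model, pooled variance U + (1 + 1/20)B.

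| Missing per arm | 2/17 | 4/17 | 6/17 |
|---|---|---|---|
| EM with arm: type I error | 0.074 | 0.114 | 0.162 |
| EM with arm: reported SE | 0.323 | 0.306 | 0.291 |
| EM with arm: true spread | 0.359 | 0.385 | 0.412 |
| EM without arm: type I error | 0.048 | 0.053 | 0.047 |
| EM without arm: estimate of a true 1.0 | 0.88 | 0.76 | 0.65 |
| EM without arm: power | 0.73 | 0.65 | 0.55 |
| Multiple imputation: type I error | 0.046 | 0.047 | 0.037 |
| Multiple imputation: reported SE | 0.361 | 0.388 | 0.426 |
| Multiple imputation: power | 0.75 | 0.69 | 0.60 |

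With arm in EM, the reported SE is too small by 1 − 0.323/0.359 = 10%, 1 − 0.306/0.385 = 21% and 1 − 0.291/0.412 = 29%. A repeat of the simulation gave type I error of 7.2%, 11.7% and 15.6% with arm in the model, and effects of 0.88, 0.77 and 0.65 without it. With the T1 score as covariate the pattern is the same: type I error 0.096, 0.130 and 0.221 with arm; effect 0.88, 0.76 and 0.63 without.

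**Step 4: check by hand.**

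- *Arm left out.* Filled-in scores carry no arm difference beyond baseline, so the effect shrinks to the observed fraction: 15/17 = 0.88, 13/17 = 0.76, 11/17 = 0.65.
- *Arm included, 4 of 17 missing.* A filled-in change score has variance (0.5−1)² = 0.25 instead of 1. The reported variance is about (13×1 + 4×0.25)/17 × 2/17 = 0.097, SE 0.31. The true variance is about 0.75×2/13 + 0.25×2/17 = 0.145, SE 0.38. Both agree with the simulation.

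**The case against.** The strongest reply is that the sentence is ambiguous. It says imputations in the plural, with EM in brackets, so the team may intend genuine multiple imputation with EM loosely attached. If so, the label is wrong and none of the numerical harm follows. That stands. The missing number of imputations, imputation model and pooling rule cannot settle it, because an article commonly leaves such detail to the full plan, and I do not count their absence as a fault.

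A reader might also draw three stronger conclusions that the documents do not support:

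- *That the ITT p-value is wrong however EM is set up.* It is not. With arm omitted, type I error stays near 5%; the harm is a diluted estimate and lost power, which is conservative.
- *That the article predicts motivation-related dropout in this trial.* Section 3 cites general research linking low motivation to dropout, as a reason to study moderators. It forecasts nothing here.
- *That the size of the error is known.* It depends on a dropout rate the article never gives. With complete T2 data there is no harm. Section 2.6.2.2 adds that the FSI-R and BITI are also routine measures, so some patients who leave the study may still have scores, although the plan does not commit to using them.

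What remains is that the article fixes a method, the only technique it names is EM, and followed literally as a single fill that technique gives invalid inference.

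**Conclusion.** The statement is wrong as written, because it equates two different procedures. The consequence is conditional on a single EM fill and on missing T2 scores. For an assumed 12%, 24% and 35% missing completely at random, 17 per arm and correlation 0.5:

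- **Arm in the EM model:** type I error of about 7%, 11–12% and 16% against a nominal 5%, with standard errors about 10%, 20% and 29% too small.
- **Arm left out:** type I error near 5%, a true 1.0 SD effect estimated at about 0.88, 0.77 and 0.65, and power of about 74%, 66% and 56%.

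The article does not say which version would apply, and the two err in opposite directions. The simulation leaves out the planned covariates other than the T1 score, and assumes equal, random loss in both arms. Loss for cyber sickness can occur only in the VR arm, so these settings need not be the worst case.

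**What to change.** Delete EM from section 2.7.1.1 and name one valid method before the data are analysed.

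- **Option A:** a likelihood-based linear mixed model on all observed T1 and T2 scores (SPSS MIXED), with condition × time as the primary test. Missing outcomes need no imputation. Patients with missing covariates or moderators (motivation, recidivism risk) would still drop out of the model, so the text must say how those are handled.
- **Option B:** genuine multiple imputation with arm, T1 score and the covariates in the imputation model and a stated number of imputations. The condition × time estimate (equivalently, the arm difference in change) is pooled by Rubin's rules, which keeps the primary test as planned.

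The change is short and stays within the named software. The cost shows in the results. Relative to a single EM fill with arm in the model, the SE at 20% missing goes from about 0.31 to 0.38, and 0.38/0.31 = 1.23, so intervals are about 23% wider. From the table the ratios are 0.361/0.323 = 1.12, 0.388/0.306 = 1.27 and 0.426/0.291 = 1.46. That is their correct width. Under true multiple imputation with 34 patients, power is about 75%, 69% and 60% at 12%, 24% and 35% missing, below the planned 80%. This loss comes from the missing data and not from the method.

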##### Secondary outcome analysis: cognitive biases and impulsivity

2.7.1.3

For secondary outcomes, separate RM-ANCOVA’s will be conducted for the BITI and the Impulsivity subscale of the FSI-R, using pre- and post-intervention scores as the within-subjects factors and treatment condition as the between-subjects factor. Additional covariates will be included as controls.

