##### Sensitivity analyses

2.7.1.5

To assess the robustness of the results, sensitivity analyses will be performed to determine how the outcomes change when different covariates are included or excluded.

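### Age falls under two covariate rules, one of them a baseline significance test, so the primary model is not fixed in advance

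*Protocol article*

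**What the plan says.** Four parts of the Protocol article bear on which covariates enter the models.

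- Section 2.7.1.1 (Preliminary analyses), as a check on randomization: "various background variables such as age, migration background, and primary diagnosis will be compared between patients in Re-ART VR and regular Re-ART". The comparison is by significance test, a t-test or a chi-square test according to the type of variable, and no significance level is given. The entry rule follows: "These variables will be included as covariates in the RM-ANCOVA if significant differences are found".
- Section 2.7.1.2 (Primary outcome analysis): "Covariates like age, motivation level, and risk of recidivism will be included to control for initial differences". No test is attached.
- Section 2.7.1.3 (Secondary outcome analysis) names none: "Additional covariates will be included as controls".
- Section 2.7.1.5 (Sensitivity analyses): "sensitivity analyses will be performed to determine how the outcomes change when different covariates are included or excluded". It does not say which set is the reference.

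The lists in 2.7.1.1 and 2.7.1.2 are both open-ended. Section 2.7.1 mentions precision as a reason to adjust, but no section selects a covariate for its relation to outcome. The stated grounds are significant differences and initial differences.

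**The concern.** A significance test of a baseline variable asks whether a difference could have arisen by chance. In a correctly randomized trial it did, so the result neither verifies the randomization nor shows which variables need adjustment. What matters for precision is how strongly a variable predicts change, and the test is blind to that.

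The article also gives age two treatments. Under one section it enters after a significant test; under the next it enters regardless. Two analysts following the text could fit different primary models to the same 34 patients. At stake are a primary analysis identifiable before the data are seen and, for variables under the testing rule, some power in a trial sized with little to spare.

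**Working it through.** **Inputs from the document (Section 2.3.1).** "Using an expected effect size (f) of 0.25, a significance level (α) of 0.05, and a desired power (1-β) of 0.80"; 34 patients, 17 per arm; two measurements; correlation 0.5 between them; ε = 1.

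**Assumptions, because the document gives no figure.** Baseline tests at 0.05 and independent of each other; outcome test at 0.05; complete data; normal covariate and change score; correlation r between covariate and change varied from 0 to 0.7.

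**1. The plan's own figure.** For the condition-by-time interaction, λ = f² × N × m / (1 − ρ) = 0.0625 × 34 × 2 / 0.5 = 8.5 on (1, 32) degrees of freedom. Power is 0.807 at N = 34 and 0.781 at N = 32, so 34 is the smallest even total and the sample size reproduces. It is not in dispute; it fixes the effect to simulate. Comparing change scores between arms of 17 gives λ = d² × 17/2 = 8.5 d², so the design effect is d = 1.0 SD of change.

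**2. The two rules for age.** Under correct randomization a 0.05 test of age is non-significant about 95% of the time. In those trials Section 2.7.1.1 leaves age out and Section 2.7.1.2 puts it in. The sections agree only in the remaining 5% or so.

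**3. Chance flags.** With the three named variables, P(at least one flag) = 1 − 0.95³ = 0.143. The tests can lead to 2³ = 8 different models.

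**4. What a test can flag at this size.** For a continuous variable the observed difference must reach t(0.975, 32) × √(2/17) = 2.037 × 0.343 = 0.70 SD. Among the named variables this applies to age. Each test flags 5% of the time however prognostic the variable is, so a prognostic variable is omitted about 95% of the time.

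**5. Consequence for the treatment test.** With two time points, the interaction test is the test of arm in a regression of change on arm. Simulated model: change = δ × arm + r × covariate + √(1 − r²) × noise, 17 per arm, 40,000 trials per setting, δ = 1.0 for power and δ = 0 for type I error. One covariate was adjusted for never, only if its baseline t-test gave p < 0.05, or always.

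| r | Power: never | Power: conditional | Power: always | Type I error: conditional | Type I error: always |
|---|---|---|---|---|---|
| 0 | 0.805 | 0.801 | 0.793 | 0.051 | 0.051 |
| 0.3 | 0.805 | 0.805 | 0.828 | 0.047 | 0.050 |
| 0.5 | 0.808 | 0.816 | 0.893 | 0.043 | 0.049 |
| 0.7 | 0.808 | 0.824 | 0.973 | 0.037 | 0.051 |

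Monte Carlo standard errors are about √(0.8 × 0.2 / 40,000) = 0.002 for power and √(0.05 × 0.95 / 40,000) = 0.001 for type I error.

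The conditional rule behaves almost like no adjustment. Its type I error falls below 5% when r > 0 because it adjusts in just the trials where a large chance imbalance would otherwise produce false positives, while the other trials keep the unadjusted standard error.

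**The case against.** The sections can be read together: Section 2.7.1.2 gives a core set, and Section 2.7.1.1 adds any background variable found unbalanced. On that reading only age is duplicated, and the purpose stated in Section 2.7.1.2 may refer back to the tests. The selection also uses baseline data only, under a rule stated in advance, and Section 2.7.1.5 will show how far results depend on covariates. Much of this stands. The conflict is confined to age, but the verb in Section 2.7.1.2 is unconditional, so it remains. The sensitivity analyses help, but they vary covariates around a primary set that is never defined.

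Four stronger readings are tempting and not supported.

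- *Every covariate waits on a test.* It does not. Motivation level and risk of recidivism enter untested through Section 2.7.1.2, and so does age on that section's wording.
- *The rule inflates false positives.* It does not; the simulation shows a nominal or slightly conservative test.
- *Most of the precision gain from covariates is lost.* That is not shown for this plan. The loss applies only to variables governed by Section 2.7.1.1, and its size rests on correlations the document does not give. At r = 0.3 it is 0.023, and at r = 0 always adjusting is slightly worse.
- *The outlier sentence in the same section* ("outliers will be examined and treated to ensure they do not bias the results") *means genuine in-range scores will be altered.* The text does not say so. An in-range value can still be an entry error, and outlier criteria are commonly left to a full protocol or SAP. It forms no part of this point.

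**Conclusion.** The point holds in a limited form. The article states a test-then-adjust rule for background variables and contradicts it for age in the next section, so it does not identify one primary model. An unseen SAP does not remove this, because the article itself states both rules.

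The baseline tests carry no useful information: a 14% chance of at least one spurious flag with three independent tests at 0.05, and about 95% omission of any given prognostic variable. The cost is forgone power and slight conservatism. Per covariate, always minus conditional adjustment is −0.008 at r = 0, +0.023 at r = 0.3 and +0.077 at r = 0.5. These figures rest on the assumed correlations, a 0.05 outcome test, one covariate and complete data. The correction is worth making because it is cheap and settles the model, not because the present rule invalidates the trial.

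**What to change.** Drop the baseline significance tests and report baseline characteristics by arm descriptively.

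Replace the covariate wording in Sections 2.7.1.1 to 2.7.1.3 with one short, closed list chosen in advance for expected prognostic value. An example is the baseline score of the outcome, age, patient motivation at T1 and risk of recidivism. (The text shown does not say when patient motivation is measured; Figure 1 may.) Use the list in every primary and secondary model whatever imbalance is observed. Confine other covariate sets, including migration background and primary diagnosis if they are not listed, to the sensitivity analyses of Section 2.7.1.5, and name the fixed list there as the reference.

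This costs a few lines of text and no new data. The statistical price is about one point of power if a listed covariate proves unrelated to outcome (0.805 unadjusted v 0.793 at r = 0), which is a reason to keep the list short with 34 patients.
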